#### Secondary outcomes

2.6.2

Anxiety and depressive symptoms will be assessed using the PHQ-4 total score (range 0–12) and two subscale scores: PHQ-2 for depressive symptoms (items 1–2; cut-off ≥3) and GAD-2 for anxiety symptoms (items 3–4; cut-off ≥3). The metric is the change from baseline (Time I) to postpartum assessment (Time III, ≥6 weeks postpartum), with mean scores compared between groups.

Childbirth-related PTSD symptoms will be assessed prenatally using the PTSD-8 total score (range 0–24; no universally established cut-off in the original instrument) at baseline (Time I), and postnatally using the PPQ-II total score and subscale scores at Time III. Mean final values will be compared between groups.

Childbirth satisfaction will be measured using the BSS-R total score at Time III, with mean final values compared between groups.

Perceived social support will be assessed using the MSPSS total score (range 12–84) and three subscale scores (Significant Other, Family, Friends; range 4–28 each) at baseline (Time I) and postpartum (Time III), with mean scores compared between groups.

Infant feeding attitudes will be measured using the IIFAS total score at baseline (Time I) and reported descriptively.

Mode of birth and obstetric outcomes will be collected via the Custom Postpartum Questionnaire (Part B) at Time III and reported as frequencies and proportions.

Although all instruments will be administered in full, not all subscales or total scores will be analysed within the scope of this trial; some data will be reserved for secondary research questions and future analyses. Detailed descriptions of all measurement instruments, including psychometric properties of Polish adaptations, are provided in section 2.12 Data Collection Methods. Formal permissions for the use of all Polish adaptations have been obtained from the respective copyright holders prior to the commencement of the study.

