### Hypotheses

1.3

The following hypotheses will be tested:

*H1*: Women in the intervention group will demonstrate significantly lower levels of PrA at 34–37 weeks of gestation compared to women in the control group receiving standard antenatal care.

*H2*: Women in the intervention group will report significantly lower levels of depressive symptoms, higher childbirth satisfaction, and better maternal and neonatal health outcomes compared to women in the control group.

*H3*: Among all randomised participants, elevated PrA at baseline will be associated with a higher likelihood of caesarean section, less favourable attitudes towards breastfeeding, and poorer maternal and neonatal health outcomes, regardless of group allocation. H3 is an exploratory hypothesis examining the association between baseline anxiety and obstetric outcomes across both groups, independent of treatment allocation.

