**Figure 1 fig1:**
[figure not shown]
CONSORT flow diagram.

**Table 2 tab2:** Schedule of enrolment, interventions and assessments (SPIRIT 2025).

Timepoint	Enrolment	Intervention period	Follow-up	Close-out
	Time I 24–30 weeks of gestation	24–34 weeks of gestation	Time II 34–37 weeks of gestation	Time III ≥6 weeks after delivery
Enrolment				
Eligibility screening	X			
Informed consent	X			
Randomisation	X			
Intervention				
Psychoeducational programme (Sessions 1–6)	X	X → → → X		
Standard antenatal care + booklet	X	X → → → X	X	X
Assessments				
Sociodemographic and clinical data (Part A)	X			
PRAQ-R2 (primary outcome)	X		X	
PHQ-4	X			X
PTSD-8	X			
MSPSS	X			X
IIFAS	X			
PPQ-II				X
BSS-R				X
Obstetric outcomes (Part B)				X

PP, postpartum; PRAQ-R2, Pregnancy-related anxiety questionnaire-revised 2; PHQ-4, Patient health questionnaire-4; PTSD-8, Post-traumatic stress disorder questionnaire; MSPSS, Multidimensional scale of perceived social support; IIFAS, Iowa infant feeding attitude scale; PPQ-II, Perinatal post-traumatic stress disorder questionnaire-II; BSS-R, Birth satisfaction scale-revised.

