#### Time I—prenatal assessment

2.12.1

The following instruments will be utilised for data collection during pregnancy:

Custom Prenatal Questionnaire (Part A): A self-report form designed to collect sociodemographic and clinical background information.Iowa Infant Feeding Attitude Scale (IIFAS) (54), Polish adaptation (55): A 16-item self-report scale used to assess women’s attitudes and beliefs towards breastfeeding and formula feeding, to predict the choice of feeding method and intended duration of breastfeeding. The Polish adaptation demonstrated acceptable psychometric properties in a sample of 401 postpartum women, with satisfactory internal consistency (Cronbach’s *α* = 0.725), confirmed two-factor structure accounting for 31.18% of variance, and discriminative power coefficients above 0.2 for all items. Subscales were strongly correlated with the total score (*r* = 0.803 for both subscales) (55).Multidimensional Scale of Perceived Social Support (MSPSS) (56), Polish adaptation (57): A 12-item self-report tool for measuring perceived social support from three sources: family, friends, and a significant other. The Polish adaptation demonstrated satisfactory psychometric properties in a sample of 1,322 adults, with confirmed three-factor structure (RMSEA = 0.065; *χ^2^*/df = 2.957) and high internal consistency (Cronbach’s *α* = 0.893 for the total score; *α* = 0.931 for Friends; *α* = 0.915 for Family; *α* = 0.865 for Significant Other), as well as satisfactory temporal stability and convergent validity (57).Pregnancy-Related Anxiety Questionnaire—Revised 2 (PRAQ-R2), Polish adaptation (26). The primary outcome measure, the PRAQ-R2, is a 10-item questionnaire that covers three subscales of anxiety specific to pregnancy and childbirth: (1) fear of childbirth, (2) worries that the child will be physically or mentally disabled, and (3) concern about one’s own appearance during pregnancy. The overall and factor scores demonstrate good reliability and validity regardless of parity. The Polish adaptation of the PRAQ-R2 demonstrated good psychometric properties in a sample of 175 Polish pregnant women. Confirmatory factor analysis confirmed the original three-factor structure (CFI = 1.00; TLI = 1.00; RMSEA < 0.001), and internal consistency was satisfactory across all subscales and the total score (Cronbach’s *α* ranging from 0.68 to 0.94). Convergent validity was confirmed through significant correlations with the Hospital Anxiety and Depression Scale (HADS) and the Visual Analogue Scale (VAS) (26).Patient Health Questionnaire-4 (PHQ-4), Polish version: A short questionnaire used in screening in primary healthcare practice and clinical settings for examining anxiety and depressive symptoms. The Polish version demonstrated good psychometric properties in a large community sample of Polish adults (*n* = 1,115), with acceptable internal consistency (Cronbach’s *α* = 0.74 for the anxiety subscale and *α* = 0.77 for the depression subscale), confirmed two-factor structure, and measurement invariance across age and gender groups (58).Post-Traumatic Stress Disorder Questionnaire (PTSD-8), Polish (59): The PTSD-8 questionnaire contains questions about stress reactions manifested as intrusion (four items), avoidance (two items) or hyperarousal (two items). It is both a diagnostic tool for PTSD and an assessment tool to evaluate the severity of this syndrome, its determinants and health consequences. The Polish adaptation demonstrated high reliability (Cronbach’s α = 0.891, McDonald’s *Ω* = 0.890) and acceptable construct validity based on confirmatory factor analysis of an adjusted single-factor model (CMIN/DF = 4.944; NFI = 0.976; RFI = 0.955; IFI = 0.981; TLI = 0.964; RMSEA = 0.073, 90% CI: 0.057–0.090). Factor loadings ranged from 0.613 to 0.760, and average variance extracted (AVE) was 0.489 (59).

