
#### Time II—post-intervention assessment

2.12.2

The second phase of data collection will consist solely of a follow-up measurement using the PRAQ-R2 to assess changes in the primary outcome.

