#### Time III—postpartum assessment

2.12.3

The following instruments will be utilised for data collection after delivery:

Custom Postpartum Questionnaire (Part B): a self-report form designed to collect supplementary interview data and clinical information following childbirth.Perinatal Post-Traumatic Stress Disorder Questionnaire-II (PPQ-II), Polish translation (60, 61): a 14-item self-report questionnaire assessing childbirth-related PTSD symptoms across two domains: Avoidance/Intrusion and Arousal. The Polish adaptation demonstrated very good psychometric properties in a sample of 273 postpartum mothers, with high internal consistency (Cronbach’s *α* = 0.92 for the total score; *α* = 0.91 for Avoidance/Intrusion; *α* = 0.86 for Arousal), confirmed two-factor structure explaining 62% of total variance (KMO = 0.90), good convergent validity with the PTSD-8 (*r* = 0.43–0.85) and DASS-21 (*r* = 0.54–0.78), and excellent temporal stability over a 3-month interval (*r* = 0.90) (61)MSPSS: as described above (Time I) (57)Birth Satisfaction Scale-Revised (BSS-R), Polish (62, 63)PHQ-4: As described above (Time I) (58)

To promote retention, reminder messages will be sent prior to each data collection time point, and research midwives will maintain contact with participants throughout the study period. Participants who discontinue the intervention but remain willing to complete follow-up assessments will be encouraged to do so. Where possible, outcome data from participants who withdraw will be retained for intention-to-treat analysis. Reasons for withdrawal and loss to follow-up will be recorded and reported.

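### The IIFAS and PTSD-8 are listed as secondary outcomes but measured only before randomisation; they are baseline variables and should be classified and used as such

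*Protocol article*

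**What the plan says.** Section 2.6.2 sets out the secondary outcomes. For feeding attitudes it says: "Infant feeding attitudes will be measured using the IIFAS total score at baseline (Time I) and reported descriptively". For post-traumatic stress it says: "Childbirth-related PTSD symptoms will be assessed prenatally using the PTSD-8 total score", at Time I, and continues: "postnatally using the PPQ-II total score and subscale scores at Time III. Mean final values will be compared between groups".

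Section 2.12.1 describes the PTSD-8 by its symptom clusters: "The PTSD-8 questionnaire contains questions about stress reactions manifested as intrusion (four items), avoidance (two items) or hyperarousal (two items". It mentions no childbirth-specific content.

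Section 1.3 says that the hypotheses listed there will be tested. H3, labelled exploratory, relates baseline pregnancy-related anxiety to several variables, among them "less favourable attitudes towards breastfeeding, and poorer maternal and neonatal health outcomes, regardless of group allocation".

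Section 2.14 says that continuous secondary outcomes will be analysed by linear regression. It names no covariates for these models.

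**The concern.** A secondary outcome of a randomised trial should be able to respond to the allocated treatment. A score taken only before allocation cannot. Any difference between arms on such a score is chance imbalance, whatever the programme does. Listing the IIFAS and PTSD-8 among the outcomes makes the list look broader than the evidence it can supply.

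Three details follow from this classification:

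- The PTSD-8 is described as a general PTSD symptom scale but is labelled childbirth-related. For a woman with no previous birth, a score at 24–30 weeks cannot carry that meaning.
- The statement about final means follows a sentence naming both the PTSD-8 and the PPQ-II, although the PTSD-8 has no final value. The PPQ-II comparison then stands with no stated baseline adjustment, while a related baseline score is already being collected.
- H3 promises a test involving breastfeeding attitudes. The only listed instrument for those attitudes is to be described, with no association analysis.

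**Working it through.** The protocol gives no figure to reproduce. The check sets the schedule against the outcome list.

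**Step 1: when each instrument is given.** The sources are Table 2 ("Schedule of enrolment, interventions and assessments (SPIRIT 2025") and sections 2.12.1 to 2.12.3. For Time II, section 2.12.2 says: "The second phase of data collection will consist solely of a follow-up measurement using the PRAQ-R2 to assess changes in the primary outcome". For Time III, the list introduced by "The following instruments will be utilised for data collection after delivery" contains Part B, PPQ-II, MSPSS, BSS-R and PHQ-4.

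| Instrument | Time I | Time II | Time III | Assessments after randomisation |
|---|---|---|---|---|
| PRAQ-R2 | yes | yes | no | 1 |
| PHQ-4 | yes | no | yes | 1 |
| MSPSS | yes | no | yes | 1 |
| PPQ-II | no | no | yes | 1 |
| BSS-R | no | no | yes | 1 |
| IIFAS | yes | no | no | 0 |
| PTSD-8 | yes | no | no | 0 |

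**Step 2: order of Time I and randomisation.** Under section 2.10, women complete the baseline assessment online and are telephoned afterwards to confirm eligibility. Under section 2.11, the allocation envelope is opened only after final consent. Section 2.10 names the PRAQ-R2 and the sociodemographic form as parts of that assessment. The IIFAS and PTSD-8 belong to the same Time I battery, and section 2.6.2 calls both baseline measures. Both scores therefore precede allocation.

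**Step 3: the childbirth-related label.** Sections 2.4.1 and 2.4.2 set no parity rule, so women with no previous birth may enrol. The description of Session 2 in section 2.5.2 provides for multiparous women, so some participants will have given birth before. In the second group the PTSD-8 may reflect an earlier birth. In the first it cannot.

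**Step 4: what the PTSD-8 could add to the PPQ-II comparison.** In a linear regression of PPQ-II on arm, adding a baseline covariate whose within-arm correlation with PPQ-II is r removes a share r² of the residual variance, apart from the one degree of freedom used. The standard error is multiplied by √(1 − r²).

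| r (assumed) | Variance removed, r² | Standard error factor, √(1 − r²) |
|---|---|---|
| 0.20 | 0.04 (4%) | √0.96 = 0.98 |
| 0.30 | 0.09 (9%) | √0.91 = 0.95 |
| 0.43 | 0.185 (18%) | √0.815 = 0.90 |

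The protocol does not give r for a PTSD-8 score in pregnancy and a PPQ-II score after birth. The 0.43 is the lower end of the 0.43–0.85 range in section 2.12.3, which is convergent validity in 273 postpartum mothers. It is used here as an example and is not a lower bound.

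**Step 5: H3.** Baseline IIFAS and baseline PRAQ-R2 are both available for every randomised woman, so an association can be estimated from data already planned. Section 2.6.2 states only a description.

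**The case against.** The strongest reply is that this is a misplaced heading and little more. Every section agrees on the timing, so there is no scheduling conflict. The IIFAS is to be described, and no arm comparison of it is announced. Section 2.6.2 says that some scores are reserved for later work. Section 2.14 provides linear regression for continuous outcomes, which could accommodate an H3 model. Covariates for exploratory secondary models are often left to a statistical analysis plan. Most of this stands, and it is why the point is minor. What remains is that the article itself fixes the classification, says that H3 will be tested, and then states only a description of the instrument that H3 needs.

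Several stronger readings are tempting, and the documents do not support them:

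- A reader might infer that the PTSD-8 precedes any birth and so never concerns childbirth. Multiparous women are eligible, so this is true only of the index birth.
- A reader might infer that neither scale can serve any aim of the trial. The baseline IIFAS can serve exploratory H3 as a cross-sectional association, and the PTSD domain has a valid postpartum outcome in the PPQ-II.
- A reader might infer that change from PTSD-8 to PPQ-II will be computed. Section 2.6.2 specifies change for the PHQ-4 but final values for the PTSD domain.
- A reader might take 18% as the least that adjustment would gain. The correlation behind it comes from postpartum women, and the correlation across the index birth could be lower.

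**Conclusion.** The point holds as a matter of classification and use. Two listed secondary instruments have no assessment after randomisation, so they are baseline variables and cannot show an intervention effect. This rests on the schedule alone and needs no numerical assumption beyond the Time I battery being completed before allocation, as sections 2.10 and 2.11 describe.

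The adjustment of the PPQ-II is an improvement that costs nothing to collect. The absence of a named covariate is not an error in itself. On the illustrative range above, the standard error would fall by about 2% to 10%, depending on a correlation that the documents do not give.

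The primary endpoint, its ANCOVA and the sample size are unaffected. The effect on the trial's main conclusions is minor.

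**What to change.** In section 2.6.2:

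1. List the IIFAS and PTSD-8 as baseline measures, and name the latter baseline post-traumatic stress symptoms.
2. Limit the comparison of final values to the PPQ-II, analysed by linear regression on arm with the baseline PTSD-8 score as a covariate.
3. For H3, state that the IIFAS score is regressed on the continuous baseline PRAQ-R2 score across all randomised women and read as an exploratory cross-sectional association.

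These changes need only wording and one added model term, with no new data.

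Optionally, if feeding attitudes are meant as an outcome of the programme, repeat the 16-item IIFAS at Time III and compare arms adjusted for the Time I score. That costs 16 more online items per woman at the postpartum survey.

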**Materials and methods:**

This is a two-arm, parallel-group randomised controlled trial with a 1:1 allocation ratio. A total of 74 low-risk pregnant women with elevated pregnancy-related anxiety (PRAQ-R2 score ≥30 points) will be recruited from antenatal clinics, childbirth education schools and online platforms. The intervention group will receive four to six individual psychoeducational sessions delivered by a trained midwife between 24 and 34 weeks of gestation, focusing on childbirth education, pain management, communication skills, birth planning and anxiety management techniques. The control group will receive standard antenatal care and an informational booklet. The primary outcome is the reduction in pregnancy-related anxiety levels measured via the Pregnancy-Related Anxiety Questionnaire – Revised 2 between 34 and 37 weeks. Secondary outcomes include actual mode of birth and childbirth satisfaction, as well as maternal and neonatal health outcomes. Data will be collected at three time points and analysed using intention-to-treat principles.

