A single-centre pilot study conducted among low-risk pregnant women in Poland found that more than half of participants (56%) scored at or above 30 points on the PRAQ-R2, indicating elevated PrA (38). This figure, while derived from a non-representative sample, provides the only available Polish-specific estimate of PrA prevalence and supports the clinical relevance of the present intervention within this population.

Additionally, women with greater financial resources are increasingly paying for private maternity care to ensure its continuity, establish a relationship with a midwife and minimise the risk of mistreatment—highlighting systemic shortcomings in publicly funded care. There is also evidence that insufficient knowledge and low confidence in pregnancy and childbirth-related knowledge among young Polish women are associated with higher levels of fear regarding childbirth and a preference for caesarean section, suggesting the need for prenatal education as a component of fear-reduction strategies (39).

Therefore, reducing the level of fear of childbirth in Poland is a matter of urgent public health concern. The high caesarean section rate carries significant health implications for both women and children, including increased short and long-term complication-related risks, prolonged recovery time, a higher risk of complications in subsequent pregnancies, and the so-called domino effect, where one caesarean delivery elevates the probability of the procedure being repeated in future births (30).

In its 2018 guidelines, WHO explicitly recommends the identification of pregnant women with high levels of childbirth-related anxiety and the implementation of interventions aimed at reducing this anxiety. The goal of these measures is to improve the quality of the birthing process among the population of low obstetric-risk pregnant women (6, 29, 30).

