#### Exclusion criteria

2.4.2

Women will be excluded from the study if they meet any of the following criteria: absolute or strong medical indication for caesarean delivery (e.g., placenta praevia); multiple pregnancy; diagnosis of a severe psychiatric disorder (e.g., active psychosis, schizophrenia, bipolar disorder) that could interfere with informed consent or study participation; current pharmacological treatment for anxiety or depression, regardless of symptom severity, as concomitant psychotropic medication may confound the assessment of intervention effects; concurrent participation in another structured psychological intervention; or inability to commit to the study schedule.

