*Session 1*: Initial assessment and relationship building aims to establish contact, identify sources of anxiety and measure the baseline level of anxiety. In the introductory part, the midwife presents the purpose and principles of the intervention, ensuring confidentiality and an atmosphere of trust. Next, she conducts a diagnostic interview with open-ended questions regarding the patient’s fears, experiences and expectations, for example: “What are you most afraid of regarding childbirth?,” “Do you have previous childbirth experiences?,” “How do you remember them?,” “How does anxiety affect your daily functioning?.” At the end of the session, the midwife discusses and agrees upon the topics of subsequent sessions with the participant and provides educational materials, such as a programme leaflet and a notebook for recording thoughts and questions.

*Session 2*: Education on the course of childbirth is focused on increasing knowledge about the physiology of childbirth and verifying myths and misconceptions. The midwife discusses the stages—first, second and third—of childbirth in detail, explaining the symptoms, duration of each phase and standard medical procedures used at each stage (examinations, CTG monitoring, etc.). During the conversation, she addresses specific fears revealed earlier by the patient, providing comprehensive answers and correcting inaccurate information. In the case of multiparous women, a detailed interview is conducted regarding previous births, identifying difficult experiences and jointly seeking solutions and strategies with the midwife. The session is supported by materials such as brochures on the course of childbirth, anatomical diagrams and recommended educational videos.

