### Statistical analysis plan

2.14

Analyses will be conducted according to randomised group allocation and will primarily follow the intention-to-treat principle, insofar as outcome data are available. The primary endpoint is PrA measured using the PRAQ-R2 at 34–37 weeks’ gestation. The primary analysis will compare post-intervention PRAQ-R2 scores between groups using analysis of covariance (ANCOVA), with treatment group as the main factor and baseline PRAQ-R2 score as a covariate. The primary outcome is assessed at two prenatal time points only: baseline and post-intervention. The postpartum assessment applies exclusively to secondary outcomes.

Secondary outcomes will be analysed using regression models appropriate to outcome type, with logistic regression for binary outcomes and linear regression for continuous outcomes. Secondary analyses will be considered supportive and exploratory; no formal adjustment for multiplicity is planned. Missing data will be described by study arm and time point. The primary analysis assumes data are missing at random (MAR); this assumption will be examined via sensitivity analysis, using a mixed-effects model for repeated measures applied to all available longitudinal data. Multiple imputation is not planned. The possibility of data missing not at random (MNAR) cannot be excluded and is acknowledged as a limitation. Stratification variables included in the randomisation will be entered as covariates in the primary ANCOVA model. A supportive per-protocol analysis will also be conducted among participants with observed primary endpoint data; in the intervention arm, this will additionally require completion of at least four intervention sessions. Two pre-specified sensitivity analyses will be conducted: (1) a linear mixed-effects model including midwife as a random effect, to account for potential clustering by intervention deliverer; and (2) a mixed-effects model for repeated measures applied to all available longitudinal data under a missing-at-random assumption, to assess the robustness of findings in the presence of incomplete data.

The mode of intervention delivery (in-person versus remote) will be recorded. As the trial is not powered for formal moderator analyses, any comparison by delivery mode will be considered exploratory and interpreted cautiously.

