## Expected results

5

Based on evidence from comparable psychoeducational interventions and Polish normative PRAQ-R2 data, we anticipate that women in the intervention group will demonstrate a clinically meaningful reduction in PrA at 34–37 weeks of gestation compared to the control group. Secondary outcomes are expected to show improved childbirth satisfaction, lower rates of elective caesarean section without medical indication, and better postpartum psychological wellbeing. These expectations will be formally tested in the trial.

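### The protocol gives three different accounts of how mode of birth is analysed, and none adjusts for parity or previous caesarean, a predictor it names itself.

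*Protocol article*

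**What the plan says.** The abstract lists mode of birth as a secondary outcome: "Secondary outcomes include actual mode of birth and childbirth satisfaction". Three places then describe how it is handled.

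- Section 2.6.2 (Secondary outcomes): mode of birth and the obstetric outcomes are to be "collected via the Custom Postpartum Questionnaire (Part B) at Time III and reported as frequencies and proportions". In the same section PHQ-4, PPQ-II, BSS-R and MSPSS are each to be compared between groups. Mode of birth is not.
- Section 2.14 (Statistical analysis plan): "Secondary outcomes will be analysed using regression models appropriate to outcome type, with logistic regression for binary outcomes". No covariates are listed for these models. The same section calls secondary analyses supportive and exploratory.
- Section 5 (Expected results) anticipates a lower rate of elective caesarean without medical indication, among other things, and adds: "These expectations will be formally tested in the trial".

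On obstetric history, section 1.1.4 (Polish context) describes a domino effect "where one caesarean delivery elevates the probability of the procedure being repeated in future births". Section 2.5.2 (Intervention) shows that parous women take part: "In the case of multiparous women, a detailed interview is conducted regarding previous births". The exclusion in section 2.4.2 reads "absolute or strong medical indication for caesarean delivery (e.g., placenta praevia" and does not name previous caesarean.

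Section 2.11 describes block randomisation without naming a stratification factor. Section 2.14 refers to stratification variables, also unnamed, and enters them in the primary ANCOVA only.

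**The concern.** A reader cannot tell whether caesarean birth will be tabulated, modelled or formally tested. The outcome carries much of the trial's rationale: it appears in the abstract, the specific objectives (1.2) and the policy argument in the Discussion. If the choice stays open until the data are in, a table, a crude test and an adjusted model are all defensible from the text.

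Separately, the protocol identifies a characteristic fixed before randomisation that predicts the outcome, and then leaves it out of every stated analysis of that outcome. With 37 women per arm, the arms can differ by several women with a previous caesarean through chance alone. An adjusted analysis accounts for such a difference. A crude one leaves it in the estimate and in the noise.

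**Working it through.** **The three statements side by side.** A table of frequencies (2.6.2) is a way of reporting and is compatible with a model reported elsewhere. Logistic regression (2.14) is an analysis, and caesarean yes/no is binary. A formal test (section 5) is stronger than an exploratory, supportive analysis (2.14). Sections 2.6.2 and 2.14 could be read together, but 2.6.2 omits the between-group comparison it states for other secondary outcomes, and section 5 does not fit the exploratory label. None of the three mentions obstetric history.

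**The plan's own figures.** The protocol gives no effect size, power or sample size for mode of birth, so there is no figure to reproduce. The calculation for the primary outcome is not used here.

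**Inputs.**
- From the documents: 37 women per arm (2.9); national caesarean rate 48.4% in 2025 (1.1.4), used as a proxy for the overall rate.
- Assumed, not in the documents: share *s* with a previous caesarean, 10-30%; caesarean risk *c* in those women, 80-90%.

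**Step 1: risk in the other women**, holding the overall rate at 48.4%: p0 = (0.484 - s·c)/(1 - s).
- s = 0.10, c = 0.80: (0.484 - 0.080)/0.90 = 0.449, a risk gap of 0.351.
- s = 0.30, c = 0.90: (0.484 - 0.270)/0.70 = 0.306, a risk gap of 0.594.

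**Step 2: shift in the crude difference per 10 points of imbalance** = 0.10 × risk gap, which is 3.5 to 5.9 percentage points.

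**Step 3: how often such an imbalance arises.** The number of previous-caesarean women falling in one arm is hypergeometric (74 women, 37 per arm):

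| Share | Women among 74 | Chance of imbalance ≥10 points |
|---|---|---|
| 10% | 7 | 11% |
| 15% | 11 | 19% |
| 20% | 15 | 25% |
| 30% | 22 | 45% |

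**Step 4: ordinary sampling error.** SE of the crude difference = sqrt(2 × 0.484 × 0.516/37) = 0.116. The 95% half-width is 1.96 × 0.116 = 0.228, about 23 points (25 points with 31 per arm).

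**Step 5: precision.** The share of outcome variance explained is R² = s(1 - s)·gap²/(0.484 × 0.516).
- Low end: 0.09 × 0.351²/0.2497 = 0.044.
- High end: 0.21 × 0.594²/0.2497 = 0.297.

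Multiplying the half-width by sqrt(1 - R²) gives about 22.3 points at the low end and 19.1 at the high end.

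**Step 6: simulation**, 100,000 trials per scenario with 37 per arm, comparing a crude two-proportion test with a test stratified by previous caesarean:

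| Share, repeat risk | Type I error, crude, all allocations | Type I error, crude, imbalance ≥10 points | Type I error, stratified, imbalance ≥10 points | Power at OR 0.4, crude | Power at OR 0.4, stratified |
|---|---|---|---|---|---|
| 15%, 80% | 4.7% | 6.4% | 4.8% | 40% | 43% |
| 15%, 90% | 4.8% | 8.0% | 4.9% | 35% | 40% |
| 20%, 90% | 4.8% | 8.7% | 4.8% | 31% | 38% |
| 30%, 90% | 4.7% | 7.8% | 4.8% | 23% | 33% |

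The OR is within stratum. Under no effect, the mean crude difference over all allocations is 0.

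**The case against.** The strongest reply is that the plan already covers this: 2.6.2 describes reporting, 2.14 describes analysis, and covariates for an exploratory secondary model are commonly left to a fuller analysis plan. Part of this stands. Logistic regression is stated, so a reader who infers from 2.6.2 that raw frequencies are the only plan goes further than the document allows. The exploratory label also limits how much rests on the result. But section 5 promises a formal test. The article says elsewhere that its full protocol and analysis plan are published within it, with supplementary details on request. It also names several other candidate covariates (antenatal education, partner attendance, outside psychoeducational support, recruitment source), but not the one it links to repeat caesarean.

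Three stronger readings are tempting and are not supported.

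- *The crude comparison is biased.* It is not. Chance imbalance is already part of the sampling error in Step 4, and type I error over all allocations is 4.7-4.8%. The distortion is conditional on an unlucky allocation.
- *Randomisation is not balanced on previous caesarean.* This is not shown. Stratification variables are mentioned in 2.14 but never named.
- *Obstetric history is collected only in the intervention arm.* Session 2 takes a detailed history there, but Part A collects clinical background from every woman at Time I and may already include parity and previous caesarean.

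It is also fair that the size rests on assumed shares and risks, that the exclusion for strong medical indication may remove some women with a previous caesarean, and that adjustment is not free in a sample this small.

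**Conclusion.** The point holds in a moderate form. Sections 2.6.2, 2.14 and 5 do not agree on how mode of birth is analysed and must be reconciled. Whichever is meant, no adjustment for parity or previous caesarean is named.

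Without adjustment the comparison remains valid on average but loses precision. Power is about 3 to 10 percentage points lower at a within-stratum OR of 0.4, for assumed shares of 15-30%. An imbalance of at least 10 points has an 11-45% chance, and each 10 points moves the caesarean difference by about 4 to 6 points, for shares of 10-30% and repeat risks of 80-90%. These shifts are well below the 95% half-width of about 23 points, so adjustment will not make this trial decisive on caesarean birth. It is a sensible improvement to an exploratory secondary outcome and does not affect the primary analysis.

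**What to change.** In 2.6.2 and 2.14, state one analysis: caesarean birth is compared by randomised arm with logistic regression adjusted for baseline obstetric history in three levels (nulliparous; parous without caesarean; parous with caesarean). Report a standardised risk difference with 95% CI beside the raw proportions, and label the analysis exploratory and secondary. Bring section 5 into line by removing or qualifying the claim of formal testing.

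State in advance that a penalised or stratified (Mantel-Haenszel) estimate is used if a level is sparse or separates. This could well happen: at a 10% share about 7 of 74 women have a previous caesarean, and the chance that all 7 have another is 0.80^7 = 21% to 0.90^7 = 48%.

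Confirm that Part A records parity and previous caesarean for every woman before randomisation, and add the item if it does not.

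The cost is a few sentences, at most one questionnaire item, two degrees of freedom in a small model and the possibility of sparse cells.
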